**Table 3. Number of patients with an SAE needed to stop the study early:**

| Number of laser treatment patients | If this many or more with an SAE, the study will be stopped | 95% LCL if this number with an SAE | 95% UCL if this number with an SAE |
|------------------------------------|-------------------------------------------------------------|------------------------------------|------------------------------------|
| 10                                 | 3                                                           | 0.103                              | 0.608                              |
| 20                                 | 5                                                           | 0.108                              | 0.473                              |
| 30                                 | 7                                                           | 0.115                              | 0.412                              |
| 40                                 | 8                                                           | 0.102                              | 0.350                              |
| 50                                 | 10                                                          | 0.111                              | 0.332                              |
| 60                                 | 11                                                          | 0.104                              | 0.301                              |
| 70                                 | 13                                                          | 0.111                              | 0.294                              |

An interim analysis is planned when a quarter of the planned total patients (26 patients in each group) have completed their 1 year follow-up and a final analysis will be performed when all patients have completed 1 year of follow up. These two analyses have been unequally spaced in order to ensure that the interim analysis is performed before study enrollment is complete. The interim analyses will be interested in assessing futility of the primary endpoint; the trial will be monitored based on the primary outcome of the proportion of patients with recurrent pilonidal disease and will employ the error spending function approach described by Lan and Demets and the error spending function described by O'Brien and Fleming.

Throughout the trial, the rate of pilonidal disease recurrence at 6 months and 1 year and the tolerance of laser treatments will be monitored for safety. Tolerance to the laser treatments will be monitored by examining for study related serious adverse events (SAE) which include severe pain (defined as a maximum pain score of 8 or above during or within 24 hours of treatment) or second degree burns. The rates of SAEs will be calculated after every group of 10 patients has completed the course of treatment. The percentage of patients with either a second degree burn or a maximum pain score of 8 or above during or after treatment will be estimated. If the lower 95% confidence limit of this proportion exceeds 10%, the trial will be stopped (see Table 3 in the Protection of Human Subjects section for the stopping threshold at each interim safety analysis). The 10% level was chosen based on input from patients involved in our feasibility and tolerability pilot in which they expressed that even if they had experienced a high pain score or minor burn, they would like to continue receiving therapy as these both are self-limited events with minimal long term morbidity. These rates will be regularly reported to the Data and Safety Monitoring Committee (DSMC).

To verify the incident of a suspected recurrence during the course of the study, staff may request that the patient consent to release their protected health information from external entities. This would require the patient or the patient's personal representative to sign an MR-9 Authorization form.

Any adverse events such as an inability to tolerate the laser therapy or a recurrence will be tracked. Since recurrence is an expected adverse event it will not be reported; however, it will be monitored and if we detect an increased rate of recurrence with laser therapy, this will be reported and the trial will be stopped. Mild to moderate pain (pain score 7 or lower) secondary to laser therapy is also consider an expected adverse event and will not be reported. SAEs due to laser treatment include severe pain (pain score 8 or higher) and deep second degree burns.

It is also possible that AE might occur that are not directly related to the study. As such, all AE will be classified as not related (clearly unrelated to study participation), possibly related (temporally related to study participation but could have been caused by other factors), or probably related (temporally related to study participation and cannot be reasonably explained by other factors) to study participation. The clinical study team will review all AE as they occur and determine the seriousness and relatedness of them.

We do not expect any severe AE in either study group. The clinical study team will review any SAE as they occur. All SAEs deemed probably related to the study (and all deaths) will be reported to the IRB within 72 hours of discovery.

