|                                                  | 
to the standard care group will be offered laser treatment. If these patients choose to receive the elective laser treatments, they will be brought back into the clinic and re-consented by the study staff prior to their first treatment. They will have the option to commit to one or two additional years in the study and will be followed in the same manner as the patients initially randomized to the laser intervention group. Data will be collected from the patients per the same follow-up surveys at 1, 2, 3, and 4 months and post-treatment follow-up surveys at 6, 9, and 12 months. Control arm participants who do not receive the elective laser treatments at the 12 month time point will continue to follow up at 18, and 24 months from the initial treatment.
 
Beginning March 16, 2020 the Abigail Wexner Research Institute halted all non-essential research study appointments in response to the COVID-19 pandemic. Laser arm patients whose treatments are delayed will have a gap between treatments longer than 4-6 weeks. This gap will vary between the 1, 2, 3, and 4 month follow-ups and some may occur during the patients 6 month, 9 month or 12 month follow-ups.
 
The gap in the laser treatments caused by COVID-19 also created a gap in when we could begin laser treatments in newly enrolled patients by 1-3 months. Since a laser patient's participation in the study begins at their first laser treatment, no data has been collected on these patients. Patients in the group have reported no longer being interested/able to receive treatments due to concerns about COVID and visits to the hospital to receive laser treatments. This group of about 15 patients was not anticipated for our sample size calculation but are needed for the primary outcomes data. In order to maintain the required power in our analyses, our statistician recommends enrolling and randomizing an additional 30 patients, thereby increasing our sample size to 302 patients (151 in each group).
 |

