| Disease-related stigma                           | X             |         |         | X       |         |         | X       |          |          |          |
| Disease-related attitudes                        | X             |         | X       |         |         | X       |         | X        |          |          |

4.2 Data will be monitored by research team members once a week to ensure that all data (clinical data and questionnaires) collected are correctly completed. The proportion of patients that have a study related SAE (second degree burn or pain score >8) will be calculated after every group of 10 patients have completed their course of treatment. If the lower limit of the 95% confidence interval for this proportion exceeds 10%, the trial will be stopped. A Data Safety and Monitoring Committee (DSMC) has been formed and will meet every 6 months throughout the period during which patients are being recruited and through their first year of follow-up. The DSMC will review data provided by the primary study statistician and other study staff involved in data management and analysis. [name] (pediatric surgeon, Seattle Children's Hospital) will act as the chairman of the DSMC, and will serve alongside [name] (pediatric surgeon, Vanderbilt) and [name] (Statistician/Researcher, Nationwide Children's Hospital). The study principal investigator will be made aware of all adverse events as they occur and a quarterly review of all adverse events (AEs) that occur in the trial will be performed by the study team. All unexpected non-serious AEs and SAEs relating to participation in the study will be reported verbally and in writing to the study PI and NCH IRB. The verbal report will occur within 48 hours of the occurrence. The written report of a SAE (e.g., death or life-threatening adverse event) will be reported within 7 days.

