## **5.0 Study Intervention/Investigational Agent**

5.1 Subjects randomized to the laser depilation arm will visit the surgery clinic for 1 treatment every 4-6 weeks to obtain a total of 5 treatments. Fitzpatrick skin type classification will be assessed during the initial visit. The Fitzpatrick skin type classification is based on the level of pigmentation of the skin and its response to ultraviolet light (See Appendix). It will be used to select the best laser to perform hair removal for each patient. The laser treatment group will consist of an 810 nm (for Fitzpatrick skin types I-IV) or Nd:YAG (for Fitzpatrick skin types V-VI) 28 joule application at auto pulse duration for 400 ms. A cooling platform and application of 7% lidocaine/ 7% tetracaine cream, applied 45 minutes prior to treatment, will minimize any discomfort associated with the heat of the laser treatments.

The two lasers that will be used in this study (810 nm or Nd:YAG) are both FDA approved for hair removal in all areas of the human body including the back and perineum. Pilonidal disease is not an FDA approved indication for laser hair removal; however, it is being performed commonly in clinical practice. It was determined, by the Director of the Drug and Device Development Services and the Institutional Review

Board (IRB) at NCH that an investigational device exemption is not necessary because we are using an approved device for investigational purposes with non-significant risk. Laser use in this study poses minimal risk to the patient and these minimal risks are similar to the risks associated with hair removal in other regions of the body for which these devices are already FDA approved. Furthermore, our institutional pilot study confirmed the safety and tolerability of these specific laser machines in an adolescent and young adult population.

5.2 Drug/Device Handling: If the research involves drugs or device, describe your plans to store, handle, and administer those drugs or devices so that they will be used only on subjects and be used only by authorized investigators. N/A – We are using a approved device for investigational purposes with non-significant risk.

- If the control of the drugs or devices used in this protocol will be accomplished by following an established, approved organizational SOP (e.g., Research Pharmacy SOP for the Control of Investigational Drugs, etc.), please reference that SOP in this section. – N/A

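### The laser-harm limit is read only after each ten patients finish a 16–24 week course, though for a fixed group a count that reaches its Table 3 row already decides the look

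*Combined protocol and SAP*

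**What the plan says.** Section 4.2 states the timing twice. The SAE proportion "will be calculated after every group of 10 patients have completed their course of treatment", and, below Table 3, "The rates of SAEs will be calculated after every group of 10 patients has completed the course of treatment". The criterion is: "If the lower 95% confidence limit of this proportion exceeds 10%, the trial will be stopped".

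Table 3 turns this into counts at 10, 20, … 70 laser patients, under the column head "If this many or more with an SAE, the study will be stopped". The quantity that 4.2 estimates is counted once per patient over the whole course: "The percentage of patients with either a second degree burn or a maximum pain score of 8 or above during or after treatment will be" …

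Section 5.1 sets the course as "1 treatment every 4-6 weeks to obtain a total of 5 treatments". The Study Summary adds, for the pandemic closure: "Laser arm patients whose treatments are delayed will have a gap between treatments longer than 4-6 weeks".

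Information on events arrives much sooner. Section 6.4 has pain rated immediately and 24 hours after each session, and 6.3 has a surgeon assess each patient before and after treatment. Section 4.2 says "The study principal investigator will be made aware of all adverse events as they occur". It also provides weekly data checks, quarterly adverse event review, reports to the IRB and DSMC meetings every six months.

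**The concern.** This is the only quantitative harm rule for laser treatment. A patient who has had an SAE cannot later become a patient who has not. So once the patients forming a group are settled and enough of them have had an SAE, the rest of the group can only confirm the result. The plan nevertheless waits for the whole group to finish. Meanwhile adolescents continue to receive laser sessions, and new ones start, after the plan's own limit has in substance been met.

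A second problem follows from the same wording. Because groups consist of patients who completed the course, a patient who stops laser because of an SAE may never enter the count.

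**Working it through.** **1. Table 3 reproduced.** The Agresti–Coull interval, with z = 1.96 and z² = 3.8416, gives the table. With ñ = n + z² and p̃ = (x + z²/2)/ñ, the limits are p̃ ± z√(p̃(1 − p̃)/ñ).

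For 3 of 10: ñ = 13.8416; p̃ = 4.9208/13.8416 = 0.3555; half-width = 1.96 × √(0.3555 × 0.6445/13.8416) = 0.252; limits 0.103 and 0.608, as printed.

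For 2 of 10: p̃ = 3.9208/13.8416 = 0.2833; half-width 0.237; lower limit 0.046, so no stop.

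All seven rows (3/10, 5/20, 7/30, 8/40, 10/50, 11/60, 13/70) are the smallest count with a lower limit above 0.10, and all 14 printed limits agree within 0.001.

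**2. When a look is decided.** With n fixed, the lower limit rises with x, and x cannot fall. Once x reaches the Table 3 number within that group, no later result in the group can reverse it.

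**3. Length of the wait built in.** Five sessions have four gaps: 4 × 4 = 16 weeks to 4 × 6 = 24 weeks from first to last session.

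**4. Other reviews, set side by side.**

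| Review in the protocol | When | Tied to a Table 3 count? |
|---|---|---|
| Principal investigator and study team, SAEs | as they occur | no |
| Adverse event review | quarterly | no |
| DSMC meeting | every 6 months | no |
| SAE proportion against the 10% limit | after each 10 completed courses | yes |

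**5. How often the rule would stop the trial.** This is an exact binomial recursion over the seven published looks: at each look add a Binomial(10, p) count, remove the paths at or above the row, and sum what was removed.

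| True SAE rate per patient | Chance of stopping by 70 patients |
|---|---|
| 5% | 1.3% |
| 10% | 12.5% |
| 15% | about 45% |
| 20% | 79.7% |
| 30% | 99.5% |

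**6. Size of the wait, by simulation.** From the protocol: 151 laser patients, session gaps of 4–6 weeks (taken as uniform) and Table 3 to n = 70 only. Assumed, because the documents do not give them: 2–6 laser starts per month, a true SAE risk of 15–30% per patient, and equal risk at each session. The wait runs from the first time a group ordered by first session reaches its row to the completion-based look that stops the trial. Ranges across scenarios, among trials that stop:

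- mean wait about 8–17 weeks;
- about 34–68 further laser sessions;
- about 7–15 new laser starts;
- wait under four weeks in about 7–26% of stopping trials.

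By the first look about 19–39 patients have already started laser, that is 19/151 = 13% to 39/151 = 26% of the arm. Equal risk per session is the milder assumption. If SAEs occur at the first session, the median wait is 21–27 weeks (2–8 starts per month, 20–40% risk).

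**7. Effect of forming groups by completion.** If every patient completes, overall stopping chances under completion order and first-session order agree within simulation error, though up to about 4% of individual trials decide differently. If half of the patients with an SAE before session five leave (an assumption), the chance of stopping by 70 at a 20% SAE rate is about 28% when only completers count and about 79% when everyone who started counts.

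**The case against.** The strongest objection concerns the word fixed. Under the protocol's wording, membership of a group is settled by completion, so during treatment it is not yet known who the first ten completers will be. A reader might infer that three SAEs anywhere among treated patients settle the first look, and that waiting can never change a decision. The documents do not support that. With 2–8 starts per month and a 20% SAE rate, 46–65% of simulated trials with three SAEs among all treated patients would not stop at the first look. The statement holds only for SAEs in patients who belong to that group. This stands, and it is why the remedy must define the groups.

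A reader might also infer that laser always continues for months past the limit. It need not: the wait can be zero if the deciding SAE falls at the tenth completer's last session, and accrual and SAE timing are not in the documents.

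The benefit is also conditional. The pilot reported full tolerability and no second degree burns in its 13-patient cohort, section 4.2 expects no severe events, and it describes high pain scores and minor burns as self-limited. At true rates of 5–10% the rule seldom stops the trial, and the delay seldom matters. That limits the importance of the point.

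Finally, SAEs are not ignored between looks. Case-by-case review permits action at any time, but that action is discretionary. None of it applies the limit the sponsor wrote down, so this part does not remove the concern.

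**Conclusion.** The point holds in a limited form. The plan reads its harm limit later than its own data allow, and nothing else in the protocol compares a running count with Table 3. If the true SAE risk is 15–30% and laser starts run at 2–6 per month, the mean delay is about 8–17 weeks, with some 34–68 further sessions. Those figures are averages over trials that stop and rest on assumed accrual, risk and timing. They do not use any extension of Table 3 beyond 70.

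It would go too far to say that reading the counts sooner changes only the date. That is essentially true of the overall stopping chance if all patients complete. If patients leave after an SAE, including them raises the chance of meeting the limit, because the completion-based groups may leave them out. Whether they are meant to be counted is not stated, and section 4.2 should say.

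**What to change.** In 4.2, reconcile the completion-based look with the review of SAEs as they occur:

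- Define each Table 3 group by order of first laser session, and state that patients who do not complete the course remain in their group.
- Keep a running count in REDCap of patients with an SAE in each group, read the sponsor's existing Table 3 counts as SAEs accrue, and notify the DSMC when a count is reached.
- Keep the end-of-group look for reporting the proportion and its interval.

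The 10% level, the event definition and the Table 3 numbers stay as the sponsor set them. The change concerns only when they are read and for whom.

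The cost is a few sentences and a tally; it needs no extra patients or visits. There are two downsides. The DSMC must be reachable between its six-monthly meetings. Counting non-completers also raises the chance of meeting the limit if patients with an SAE leave early (step 7 of the working gives an example), so the sponsor should make that choice knowingly.

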## **5.0 Study Intervention/Investigational Agent**

5.1 Subjects randomized to the laser depilation arm will visit the surgery clinic for 1 treatment every 4-6 weeks to obtain a total of 5 treatments. Fitzpatrick skin type classification will be assessed during the initial visit. The Fitzpatrick skin type classification is based on the level of pigmentation of the skin and its response to ultraviolet light (See Appendix). It will be used to select the best laser to perform hair removal for each patient. The laser treatment group will consist of an 810 nm (for Fitzpatrick skin types I-IV) or Nd:YAG (for Fitzpatrick skin types V-VI) 28 joule application at auto pulse duration for 400 ms. A cooling platform and application of 7% lidocaine/ 7% tetracaine cream, applied 45 minutes prior to treatment, will minimize any discomfort associated with the heat of the laser treatments.

The two lasers that will be used in this study (810 nm or Nd:YAG) are both FDA approved for hair removal in all areas of the human body including the back and perineum. Pilonidal disease is not an FDA approved indication for laser hair removal; however, it is being performed commonly in clinical practice. It was determined, by the Director of the Drug and Device Development Services and the Institutional Review

Board (IRB) at NCH that an investigational device exemption is not necessary because we are using an approved device for investigational purposes with non-significant risk. Laser use in this study poses minimal risk to the patient and these minimal risks are similar to the risks associated with hair removal in other regions of the body for which these devices are already FDA approved. Furthermore, our institutional pilot study confirmed the safety and tolerability of these specific laser machines in an adolescent and young adult population.

5.2 Drug/Device Handling: If the research involves drugs or device, describe your plans to store, handle, and administer those drugs or devices so that they will be used only on subjects and be used only by authorized investigators. N/A – We are using a approved device for investigational purposes with non-significant risk.

- If the control of the drugs or devices used in this protocol will be accomplished by following an established, approved organizational SOP (e.g., Research Pharmacy SOP for the Control of Investigational Drugs, etc.), please reference that SOP in this section. – N/A

5.3 If the drug is investigational (has an IND) or the device has an IDE or a claim of abbreviated IDE (non-significant risk device), include the following information: N/A

- Identify the holder of the IND/IDE/Abbreviated IDE. N/A
- Explain procedures followed to comply with sponsor requirements for FDA regulated research for the following: N/A

|                       | Applicable to: |                    |                                |
|-----------------------|-----------------------|--------------------|--------------------------------|
| FDA Regulation | IND Studies    | IDE studies | Abbreviated IDE studies |
| 21 CFR 11      | X              | X           |                                |
| 21 CFR 54      | X              | X           |                                |
| 21 CFR 210     | X              |                    |                                |
| 21 CFR 211     | X              |                    |                                |
| 21 CFR 312     | X              |                    |                                |
| 21 CFR 812     |                       | X           | X                       |
| 21 CFR 820     |                       | X           |                                |

